### Outcome assessments

Outcomes assessed in the ICON study include mortality, functional status, HRQoL and psychological outcomes. Relevant outcomes are assessed at 3, 12 and 24 months after ICU discharge (Table 1).

**Table 1 T1:** Outcomes assessed at each follow-up point in the Intensive Care Outcome Network (ICON) study

**Outcome**	**Instrument(s)**	**Time required **^a ^(minutes)
Health-related quality of life	SF-36	12
	EQ-5D	2
Anxiety and Depression	HADS survey	6
PTSD symptoms	PCL-C	5

SF-36, Medical Outcomes Study Short Form 36-Item Health Survey; EQ-5D, EuroQOL instrument; HADS, Hospital Anxiety and Depression Scale; PCL-C, PTSD Civilian Checklist

^a ^Derived from pilot testing

Outcomes are assessed with standardised instruments, most of which are used widely in critical care research. HRQoL will be measured by the SF-36 [21,24] and the EQ-5D [22]. The SF-36 is a comprehensive, generic 36-item questionnaire [26,27] that appears to be an acceptable, reliable and valid tool for use in the ICU population and its use for quality of life assessment following critical illness has been recommended [23,15]. The SF-36 contains 36 items to measure 8 domains: physical functioning, role limitations due to physical problems, bodily pain, general health perceptions, energy/vitality, social functioning, role limitations due to emotional problems, and mental health [21].

The EQ-5D (EuroQoL) has been proved to be a useful tool in a mixed critical care population [22]. The EQ-5D comprises two parts: the EQ-5D self-classifier and the EQ-VAS. The self-classifier is self-reported description of health problems according to a 5 dimensional classification i.e. mobility, self-care, usual activities, pain/discomfort and anxiety/depression. The EQ-VAS is a self-rated health status using a visual analogue scale (VAS). The EQ-VAS is similar to a thermometer and records perceptions of participants own current overall health. The VAS scale is graduated from 0 (the worst imaginable health state) to 100 (the best imaginable state) [24]. Two EQ-VAS will be included in the three month questionnaire pack. The first scale one will ask patients to rate their health immediately prior to their hospital admission that resulted in the ICU admission. The second scale will be used to rate their health current health status.

Anxiety and depression will be assessed by the HADS (Hospital Anxiety and Depression Scale) [25]. The HADS has been validated in the critical care population [4,9,11,26]. The HADS questionnaire contains 14 statements and scoring results in scales of 0–21 for anxiety and depression respectively. Scores of 8–10 indicate the possibility of anxiety or depression, and 11 and above indicate that these are likely to be present.

PTSD should ideally be diagnosed using consistent criteria and reliable instruments that exhibit high inter-rater reliability, are stable over time and are able to assess individual patients presenting with wide symptom variance [12]. Currently, the PTSD diagnostic gold standard remains a structured clinical interview to predefined criteria (e.g. DSM-IV). For obvious reasons, standardised interview is not always practically possible at ICU follow-up, and the administration of self-report inventories allows the identification of PTSD symptomatology. The ICON study will assess PTSD symptomatology using the PTSD checklist (civilian) (PCL-C). The PCL-C is a 17-item self-report measure of the 17 DSM-IV symptoms of PTSD assessing all core symptoms of PTSD i.e. intrusion, avoidance and hyperarousal. It takes minutes to complete and is a reliable and validated tool with excellent psychometric properties. A correlation of 0.93 between the total PCL score and structured interview with the Clinician-Administered PTSD Scale (CAPS) has been demonstrated (Blanchard et al), with a diagnostic efficiency of 0.9 versus the CAPS. A score of 45 or greater on the PCL-C has been recommended as a cut off point for high PTSD symptom load. A total PCL-C cut-off score of 50 has a sensitivity of 0.6 and a specificity of 0.99 of diagnosing PTSD when compared to Structured Clinical Interview for DSM-IV [28,29].

In the event of a patient scoring 45 or greater on the PCL-C and or 11–14 (moderate risk) or 15–21 (severe risk) on either aspect of the HADS, a standard letter will be sent to the patient's GP to highlight that they have demonstrated significant risk of PTSD and or anxiety or depression on the relevant screening tools. However, the exact inventory scores will not be given to the GP. If the patient did not consent for a warning letter to be sent to the GP in the event of a high inventory score, a standard letter will be sent to the patient instead. This letter will inform the patient that their questionnaire results were inconclusive and they are recommended to visit their GP to discuss their psychological health.

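### The same high screening score is called significant risk in the GP letter but inconclusive in the letter sent instead to patients who did not consent to GP notification

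*Protocol article*

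**What the plan says.** All of the relevant text is in the protocol article under Outcome assessments.

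- **Trigger.** The condition for any letter is this: "scoring 45 or greater on the PCL-C and or 11–14 (moderate risk) or 15–21 (severe risk) on either aspect of the HADS".
- **GP route.** A standard letter tells the GP that "they have demonstrated significant risk of PTSD and or anxiety or depression on the relevant screening tools". Exact scores are withheld from the GP.
- **Patient route.** The condition here is: "If the patient did not consent for a warning letter to be sent to the GP in the event of a high inventory score". In that case the patient is written to in place of the GP. "This letter will inform the patient that their questionnaire results were inconclusive", and it adds that "they are recommended to visit their GP to discuss their psychological health".
- **How the protocol reads HADS.** "Scores of 8–10 indicate the possibility of anxiety or depression, and 11 and above indicate that these are likely to be present".
- **How the protocol reads PCL-C.** "A score of 45 or greater on the PCL-C has been recommended as a cut off point for high PTSD symptom load".

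**The concern.** Both letters arise from the same event. The only thing that decides which is sent is whether the patient agreed to GP notification, and that choice does not change what the questionnaire showed. Yet the GP would be told that the screen indicates significant risk, while the patient would be told that the screen settled nothing.

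The patient version is also at odds with the score interpretation a few sentences earlier, which places the triggering scores on the positive side of the protocol's own cut-offs.

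At stake is what participants with high scores are told. For a patient whose GP is not notified, this letter is the only notice that the article describes. A description that understates the result could plausibly weaken the advice that follows it. The refusal concerns a letter to the GP; nothing in the article says that the patient also declined an accurate description of their own result.

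**Working it through.** No sample size, rate or error probability is involved, so there is nothing to recompute. The check is whether any score that triggers the patient letter falls in a range that the protocol itself regards as uncertain.

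**Step 1: the HADS trigger.** The two triggering bands, 11–14 and 15–21, together cover 11–21. The subscale maximum is 21, so the trigger is HADS of 11 or more, which is the same cut-off the protocol uses when interpreting the scale.

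**Step 2: the PCL-C trigger.** The trigger is 45 or more, again the cut-off named in the interpretation.

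**Step 3: bands side by side.**

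| Score | Protocol's reading | Triggers a letter? | Told to GP (consent) | Told to patient (no consent) |
|---|---|---|---|---|
| HADS 8–10 | condition possible | no | – | – |
| HADS 11–14 | condition likely; moderate risk | yes | significant risk | inconclusive |
| HADS 15–21 | condition likely; severe risk | yes | significant risk | inconclusive |
| PCL-C 45 or more | high symptom load | yes | significant risk | inconclusive |

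**Step 4: reading the table.** The one band that the protocol treats as equivocal, HADS 8–10, does not by itself lead to a letter. Every band that does lead to one is at or above a cut-off that the protocol treats as positive. The description in the patient letter therefore matches none of the scores that cause it to be sent. This includes the band labelled severe risk.

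**Step 5: the trigger sentence itself.** The clause that introduces the patient letter already calls the result a high score. Within a few lines, one result is thus described as high, as significant risk and as inconclusive.

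**The case against.** The case on the other side has four parts.

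1. **The patient is directed to care.** The sentence about the patient letter goes on to recommend a GP visit and names psychological health as the reason. Nobody is told that the result was normal. Under Exclusion criteria, patients whose life status cannot be traced for want of a GP or NHS number are left out, and under Data collection the trial office contacts the GP before mailing. A reader might infer that these patients have no safety net. The documents do not support that: the GP is not notified, but the patient is referred. This part stands.

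2. **A screen is not a diagnosis.** The article names structured clinical interview as the reference standard for PTSD, and it gives accuracy against interview at a PCL-C cut-off of 50 (sensitivity 0.6, specificity 0.99), not at 45. A reader might infer that patients are given a false result in the sense of a wrong diagnosis. That is too strong, and the conflict is sharper for HADS than for PCL-C. But unconfirmed is not the same as inconclusive. The GP wording shows that the protocol can report a positive screen without claiming a diagnosis, so this argument limits the point and does not remove it.

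3. **The letter is not shown.** The article only paraphrases it, the study has ethics approval, and how to address a recovering patient by post is partly a matter of communication. All true, and we cannot tell whether the ethics review covered this wording. The paraphrase is nevertheless explicit about what the patient will be told, and approval does not reconcile the two descriptions.

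4. **No estimate is affected.** A reader might infer bias in later scores because the action taken depends on consent. That does not follow. Honouring a refusal creates two routes whatever the letters say, and rewording would leave both in place. Planned analyses describes the psychological and quality-of-life results as largely descriptive, and no analysis by letter type is described. This objection stands in full.

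**Conclusion.** The contradiction is explicit and holds as written. The same triggering score is described in two incompatible ways according to recipient, and the patient's version also conflicts with the protocol's own score interpretation. It is a misdescribed screening result in the only notice described for patients whose GP is not notified. It is neither a missing referral nor a wrong diagnosis, and it is not a source of bias in the study's estimates.

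Its reach is every patient who meets the trigger and did not consent to the GP letter. No count can be given, because the article states neither a refusal rate nor how often the trigger is met. A reader might try to build a number from the 12% to 43% anxiety prevalence in the Background. That range comes from earlier studies, is given without a cut-off, and leaves out the depression and PCL-C parts of the trigger.

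The conclusion assumes only that the article's summary of the two letters reflects what they say.

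**What to change.** Reconcile the description of the result in the patient letter with the one in the GP letter, and both with the interpretation of HADS and PCL-C scores given earlier in Outcome assessments. The exact wording is for the clinical lead and the ethics committee; no clinical rule or threshold is proposed here. If the full protocol or the letter itself already words this differently from the article, correcting the article's summary would be enough.

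Otherwise the cost is one revised standard letter and a minor ethics notification. The design, the data collected and the analyses do not change.

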### Procedure

Lists of patients meeting the study inclusion criteria will be sent from the participating hospitals to the trial office, which then submits this list to the Office of National Statistics (ONS). The ONS then performs two checks on the data. The first check cleans the list to maximise the identification of individual patients on the ONS databases; the second check identifies the patients that have died since hospital discharge. From the list of surviving patients generated by the ONS, contact with the patient's GP is made to act as a further check to confirm that the patient is still alive. Adopting this approach will hopefully prevent a questionnaire pack being mailed to a deceased patient and unnecessary distress being caused to their relative.

The three-month mailing pack consists of an introductory letter to the study, a patient information sheet, consent form, questionnaire set and a FREEPOST envelope. If the questionnaire pack is not returned, a reminder mailing is posted four weeks later. Once a patient is enrolled into the study, they will receive further study packs at 12 and 24 months post ICU discharge as long as they are not subsequently identified as deceased by the pre-mailing ONS check. The 12 and 24 month mailing packs comprise a reminder letter of the study, the relevant questionnaire packs and a FREEPOST envelope.

Again, if the patient has not returned either pack 4 weeks after the initial mailing, a second pack will be sent. If the questionnaire packs are not returned after the second mailing, no further attempts will be made to contact the patient.

### Trial recruitment and baseline measurements

All patients discharged from all participating units will be given a generic discharge letter introducing the study to them and the possibility that they may receive a mailing from the ICON study team in the coming months. Data will be collected on patient demographics, ICU diagnosis, ICU stay, severity of illness using the Acute Physiology, and Chronic Health Evaluation (APACHE II) system [30] and APACHE II co-morbidity score.

### Sample size

The minimum target total survivor recruitment for the study would be at least 1000 survivors per year in the first year returning all questionnaires. With this sample size, the ICON study would be the largest existing prospective cohort study of long-term outcomes in ICU survivors.

### Data collection

Participating ICUs will submit monthly lists of patient names, hospital numbers, CMP numbers, dates of birth, addresses, and both hospital/ICU admission and discharge dates to the trial office. Just prior to a patient reaching the 3 months post-ICU discharge date, the trial office will contact the patient's GP to check the patient status on the relevant patient administration system and ensure eligibility for trial entry. Once it is confirmed that the patient was successfully discharged from hospital and is still alive, a three month study pack is mailed. ICNARC (Intensive Care National Research and Education Centre) will download clinical data to the study office quarterly. Unique database numbers will link these data with the ICON database, allowing record linkage studies with ICNARC. The study office will also snapshot each participating ICU every six months for staff and unit demographics.

### Data protection and PIAG approval

The data collection, storage and access rights will conform to the standards set out in the Data Protection Act 1998. In addition, an application will be made to PIAG (Patient Information Advisory Group) for "Section 60 exemption" class support to provide a basis in law for holding patient identifiable data. This is a requirement in UK law (Health and Social Care Act 2001) for all disease registries. Although the ICON study needs to hold patient identifiable data to allow checking with the ONS, any second parties wishing to use the data will only have access to anonymised information.

### Data Handling

The data from ICNARC databases, the ONS returns, the SF-36, EQ-5D, HADS and PCL-C responses will be stored in a series of linked databases. The data imported as electronic files (ICU databases and ONS records) will undergo filtering, validity and range checks before being included. Data from the paper returns will be scanned and error checked. The data will be held in off-line storage with two-tier backup.

Participating units will receive electronic mailings from the study office giving the number of patients that are currently being followed-up and the average questionnaire results of those patients who have consented to take part in the study.

### Planned analyses

Using ICU admission as the event defining the start of follow-up, Kaplan-Meier curves will be constructed to illustrate survival. Age and sex matched control data will be requested from ONS in a 1:1 ratio with the patients in the study, and a control group Kaplan-Meier curve calculated from these data. A log-rank test will be used to determine the statistical significance of any differences noted.

It is almost certain that the ICU survivors will show a decreased longevity compared with the general population, so this initial testing will only be used to validate the study by showing similar results to previous investigations. However, as this is a non-randomised study, there are many potential sources for bias. To minimise the possibility that a difference in survival is due to confounders and not a real effect of the either illness or the ICU care, further covariate analysis will be undertaken. To determine the effects of covariates on survival, the Cox proportional hazards method will be used. The covariates included in the model will be age, sex, APACHE II predicted mortality, socio-economic status (from postcodes), geographical area (4 zones north to south based on hospital location), month of discharge, and 12 broad diagnostic categories based of the organ system involved in the acute illness. These results will be presented as a table showing the relative effects of ICU care and the covariates on survival.

The data on psychological illness (anxiety, depression and PTSD symptomatology), and quality of life will be largely descriptive and will be presented in tabular form.

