**Methods/Design:**

The ICON (Intensive Care Outcome Network) study is a multi-centre, longitudinal study of survivors of critical illness. Patients will be recruited prior to hospital discharge from 20–30 ICUs in the UK and will be assessed at 3, 6, and 12 months following ICU discharge for health-related quality of life as measured by the Short Form-36 (SF-36) and the EuroQoL (EQ-5D); anxiety and depression as measured by the Hospital Anxiety and Depression Scale (HADS); and post traumatic stress disorder (PTSD) symptoms as measured by the PTSD Civilian Checklist (PCL-C). Postal questionnaires will be used.

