### Aims and objectives of the study

The ICON study aims to:

Define the longer-term outcomes of a large, representative sample of survivors of adult, general ICU care in the UK quantitatively in terms of their survival, HRQoL and psychological morbidity 3, 6 and 12 months after ICU discharge.

Compare the mortality of survivors of adult, general ICU care with age-, sex- and condition-matched populations of people who have not experienced ICU care.

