### Inclusion criteria

To be eligible for enrolment in the ICON study, participants must have experienced at least 24 hours of level three dependency care (ICU) at any time during their hospital stay and who survive until the time of hospital discharge.

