### Exclusion criteria

Patients will be excluded if they are: aged under 16 years; unable to complete questionnaires; foreign nationals; in residential care; unable or unwilling to consent; or if their life status cannot be traced (i.e. have no GP or NHS numbers).

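### Survival is timed from ICU admission although entry requires survival to hospital discharge, so a death-free stretch lowers the ICU group's mortality against controls

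*Protocol article*

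**What the plan says.** - **Time origin** (Planned analyses): "Using ICU admission as the event defining the start of follow-up, Kaplan-Meier curves will be constructed to illustrate survival". A log-rank test against 1:1 ONS controls and a Cox model follow. No delayed entry, left truncation or landmark is mentioned for either.
- **Eligibility** (Inclusion criteria): patients must have had at least 24 hours of level three care and be among those "who survive until the time of hospital discharge".
- **Controls** (Planned analyses): matched on age and sex. The article states neither the date on which a control's follow-up starts nor any requirement that the control be alive on a given date.
- **Aims**: outcomes, survival among them, are counted from a different point: "psychological morbidity 3, 6 and 12 months after ICU discharge". Comparing mortality with matched populations is the second stated aim.
- **Enrolment**: the Exclusion criteria remove those "unable or unwilling to consent". Under Procedure, "The three-month mailing pack consists of an introductory letter to the study, a patient information sheet, consent form, questionnaire set and a FREEPOST envelope". Under Data collection, "Once it is confirmed that the patient was successfully discharged from hospital and is still alive, a three month study pack is mailed".
- **Text pointing to a wider cohort**: the Abstract says "Patients will be recruited prior to hospital discharge from 20–30 ICUs in the UK". Under Procedure, the full lists of eligible patients go to ONS, where "the second check identifies the patients that have died since hospital discharge". Data Handling stores the ONS returns and mentions consenting patients separately.

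**The concern.** The clock starts before the event that qualifies a patient. Everyone in the ICU group must live through the rest of the hospital stay to be counted, so that stretch adds person-time and cannot add deaths. This is immortal time. The patient curve is flat at the start by construction, the observed death rate is diluted, and the hazard ratio changes over time for an artificial reason, contrary to the Cox assumption. Adjusting for age, sex, APACHE II predicted mortality, socio-economic status, area, month of discharge and diagnosis does not help, because the problem lies in the time axis and not in the case mix.

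What is at stake is the size of the excess mortality. The article already expects the excess to exist; what the Cox table is meant to add is the relative effect of ICU care.

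**Working it through.** The article states no hazard, hospital stay or expected ratio, so there is no figure to reproduce. The sizes below are illustrations.

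**Assumed inputs**
- Patient hazard after entry: h1 = 0.10 per year.
- Control hazard: h0 = 0.02 per year, from day 0. True ratio h1/h0 = 5.0.
- Death-free time L from ICU admission: 21 or 35 days if entry is hospital discharge; 100 or 130 days if entry is return of the three-month pack.
- Horizon T: 1 and 2 years. The article names 12 months in the Aims and 24 months under Outcome assessments, so both are shown.

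**Formulas** (L in years)
- Proportion of patients dead by T: d = 1 - exp(-h1 × (T - L)).
- Patient person-years per head: p = L + d/h1.
- Control rate: h0, because the hazard is constant.
- Observed rate ratio: (d/p)/h0.

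**Worked case, L = 21 days, T = 1**
- L = 21/365 = 0.0575.
- d = 1 - exp(-0.10 × 0.9425) = 0.0899.
- p = 0.0575 + 0.899 = 0.957.
- Rate = 0.0899/0.957 = 0.0940; ratio = 0.0940/0.02 = 4.70, which is 6% below 5.0.

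**All cases**

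| L (days) | Rate ratio, 12 months | Shortfall | Rate ratio, 24 months | Shortfall |
|---|---|---|---|---|
| 21 | 4.70 | 6% | 4.84 | 3% |
| 35 | 4.50 | 10% | 4.74 | 5% |
| 100 | 3.59 | 28% | 4.26 | 15% |
| 130 | 3.18 | 36% | 4.05 | 19% |

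**Does the Cox model remove it?** No. Solving the Cox score equation in the large-sample limit, with equal groups and the same hazards, gives 4.71, 4.51, 3.62 and 3.20 at 12 months and 4.85, 4.75, 4.30 and 4.09 at 24 months.

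**Sensitivity to the hazards.** Hazards of 6% against 2%, or 15% against 3%, give nearly the same proportional shortfall. So does a separate grid with control 12-month mortality of 2-5% and true ratios of 1.5 to 3. At 12 months the observed ratio is there about 91-92% of the true one for a one-month stretch, 74-75% for three months and 66% for four.

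**Absolute mortality.** The Background cites 12-month mortality of 35% to 43%. If that is taken as counted from ICU admission with a constant hazard (both assumed), the 12-month figure becomes 1 - (1 - m)^((12 - L)/12), with L in months. This gives 33-40% for one death-free month, 28-34% for three and 25-31% for four.

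**The case against.** **Which cohort is analysed.** A reader might infer that the death-free period certainly runs to three months, since consent is an entry condition and the form comes in a pack sent only to patients confirmed alive. The documents do not establish this. All listed hospital survivors go to ONS, their deaths after discharge are identified, ONS returns are held as data, and the Abstract places recruitment before discharge. If the survival cohort is all traced hospital survivors, deaths between discharge and three months count, and only the shorter stretch is immortal. This objection stands: the larger figures are conditional.

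**Control start date.** That controls are at risk from day 0 is an inference, and an article may leave the index date to a fuller document. If controls also had to be alive on the patient's discharge date, the Cox and log-rank comparisons would be largely protected. Nothing in the text says so, and the patient curve would still start too early.

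**Validation.** A reader might infer that the planned check against earlier mortality studies must fail. The documents do not support that. It depends on the time origins of cited studies that are not shown. Deaths before discharge are also excluded by eligibility, whichever clock is used.

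**Direction and consequence.** The bias is conservative, and the article calls reduced longevity almost certain. A reader might infer that the excess could vanish. In the grid above the 12-month ratio reaches about 1.0 only with a true ratio of 1.5 and four immortal months, a length that presupposes the restricted cohort. The psychological and quality-of-life results are untouched, and the origin can be reset at analysis without loss of data. All of this lowers the severity. It does not make ICU admission a suitable origin for a cohort of hospital survivors.

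**Conclusion.** The point holds and should be corrected, though it does not threaten the study. That patients have a death-free stretch from ICU admission to hospital discharge follows directly from the stated origin and the inclusion criterion. Under the assumed hazards and a 21 to 35 day stretch, and with controls at risk from the start, the ratio is understated by 6-10% at 12 months and 3-5% at 24 months. If, and only if, the survival cohort is confined to patients enrolled through the three-month pack, an assumed 100 to 130 days gives 28-36% and 15-19%. The direction is the same under both readings. The expected excess mortality would very probably still be seen; its size, which serves a stated aim and is to be reported in the Cox table, would be too small.

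**What to change.** Replace the sentence on the start of follow-up with: *Survival time starts at the date of hospital discharge; each matched control starts follow-up, alive, on the same calendar date.*

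State which cohort enters the survival analysis, all ONS-traced hospital survivors or enrolled patients only, and reconcile the Abstract with Procedure and Data collection on when recruitment takes place. If only enrolled patients are analysed, use delayed entry at the enrolment date for the patient and for the matched control.

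The Aims count from ICU discharge. That origin alone would leave the stretch up to hospital discharge immortal, so if it is kept as the time scale, it needs delayed entry at hospital discharge.

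Cost: a sentence or two of text. Hospital and ICU admission and discharge dates are already on the monthly lists described under Data collection, so no new patient data and no extra patients are needed. The ONS control request must carry the index date.

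### One sampled control per patient gives an imprecise mortality ratio, and an unstratified log-rank test ignores the age-sex matching; stratify the test and add observed versus expected deaths

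*Protocol article*

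**What the plan says.** The Aims section of the protocol article sets two aims. The second is to "Compare the mortality of survivors of adult, general ICU care with age-, sex- and condition-matched populations of people who have not experienced ICU care".

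Planned analyses gives the method. Kaplan-Meier curves are drawn for the patients and for a control group: "Age and sex matched control data will be requested from ONS in a 1:1 ratio with the patients in the study". Then: "A log-rank test will be used to determine the statistical significance of any differences noted". No stratification or pairing is mentioned, and no population-rate comparison is planned for mortality.

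The section limits what the test is for. It states that "It is almost certain that the ICU survivors will show a decreased longevity compared with the general population", and that "this initial testing will only be used to validate the study by showing similar results to previous investigations".

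A Cox model follows: "The covariates included in the model will be age, sex, APACHE II predicted mortality, socio-economic status (from postcodes"), then geographical zone by hospital location, month of discharge and 12 diagnostic categories of the acute illness. Its output is described so: "These results will be presented as a table showing the relative effects of ICU care and the covariates on survival".

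The Sample size section gives a minimum of 1000 survivors returning all questionnaires. It states no precision or power target for the mortality comparison.

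**The concern.** If a difference is taken as given, its p-value tells the reader little. What the second aim needs, and what a check against previous studies needs, is the size of the excess with an interval. A ratio estimated against one sampled control per patient carries the sampling error of a small number of control deaths. Age and sex are the only factors the controls are matched on, and population death rates supply those with practically no sampling error.

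A second and separate matter is that the controls are matched on two strong predictors of death, yet the stated test takes no account of this. The two matters have different effects and should not be merged.

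**Working it through.** **Nothing to reproduce.** The target of 1000 comes without alpha, power, hazard ratio, control mortality or event count. Control deaths are therefore assumptions throughout. The one mortality figure in the document is the 35% to 43% at 12 months in the Background. The enrolled cohort must survive to hospital discharge, so lower values are also shown.

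**Ratio scale.** With d1 patient deaths and d0 control deaths, SE(log ratio) ≈ √(1/d1 + 1/d0). With population rates treated as known, it is √(1/d1). The quotient of the two is √(1 + d1/d0), which does not depend on the number of pairs.

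| d1 | d0 | SE, 1:1 controls | SE, population rates | Quotient |
|---|---|---|---|---|
| 100 | 20 | √(0.010 + 0.050) = 0.245 | 0.100 | 2.4 |
| 200 | 40 | √(0.005 + 0.025) = 0.173 | 0.071 | 2.4 |
| 350 | 10 | 0.321 | 0.053 | 6.0 |
| 350 | 30 | 0.190 | 0.053 | 3.6 |
| 350 | 50 | 0.151 | 0.053 | 2.8 |
| 100 | 10 | 0.332 | 0.100 | 3.3 |
| 100 | 50 | 0.173 | 0.100 | 1.7 |

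The rows with 350 deaths are 1000 patients at 35% mortality, with control mortality of 1%, 3% and 5%. For 100 versus 20 deaths (ratio 5), the 95% interval is 5 × exp(±1.96 × 0.245) = 3.1 to 8.1 with 1:1 controls, and 5 × exp(±1.96 × 0.100) = 4.1 to 6.1 with population rates.

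**Risk-difference scale.** SE = √(p1q1/n + p0q0/n), n = 1000. At p1 = 35% the patient term alone gives √(0.35 × 0.65/1000) = 1.51 percentage points. Adding controls at 1% to 5% gives 1.54 to 1.66, which is 2% to 10% more. At p1 = 10% the increase is 5% to 24%. In the least favourable case tried, 5% versus 3%, it is 27%.

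**Effect of ignoring the matching on the estimate.** The simulation used 300 data sets per row, 1000 matched pairs and one year of follow-up. Assumptions: mean age 60, SD 15; log hazard rising 0.09 per year of age and 0.4 for sex. Entries are the mean log hazard ratio (empirical SD).

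| True | Unpaired | Cox with age and sex | Stratified by pair | Population rates |
|---|---|---|---|---|
| 1.099 | 1.074 (0.225) | 1.143 (0.236) | 1.145 (0.247) | 1.108 (0.125) |
| 1.609 | 1.504 (0.206) | 1.629 (0.215) | 1.632 (0.245) | 1.601 (0.093) |
| 2.303 | 2.081 (0.199) | 2.325 (0.206) | 2.323 (0.244) | 2.297 (0.070) |
| 2.996 | 2.553 (0.181) | 3.008 (0.192) | 3.005 (0.240) | 2.994 (0.050) |

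The unpaired estimate is pulled toward the null by 2% on the log scale in the first row (1.074/1.099 = 0.98) and by 15% in the last (2.553/2.996 = 0.85). Its spread is no larger than that of the age-sex Cox model. Stratifying by individual pair gives the largest spread of the four.

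**Effect on the test.** In a second simulation (1000 pairs, two years, age SD 16, log hazard slope 0.095 per year), mean Z for the unstratified log-rank against one stratified by five-year age band was 2.26 against 2.50, 3.89 against 4.34, and 6.62 against 7.59, at hazard ratios 1.5, 2 and 3. The squared quotients are 0.82, 0.80 and 0.76. Repeat runs stratified by age and sex gave 0.75 to 0.83. In one of them the SD of Z at hazard ratio 1.5 was 0.94 unstratified and 1.03 stratified, so the unstratified test is scaled too conservatively. The squared quotient mixes this with the attenuation and is not a pure loss of information.

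**Detection.** Power of the 1:1 comparison at an assumed two-sided 5% level exceeds 0.95 in every scenario tried except 5% versus 3% mortality, where it is 0.63 to 0.64.

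**The case against.** The plan gives the log-rank test a limited job, confirming an expected difference, and in nearly every scenario it has ample power for that. A reader might infer that the study could miss the excess mortality; the figures do not support this. The answer is only partial, though. Agreement with previous studies is judged on an estimate, and an interval of 3.1 to 8.1 agrees with a great deal.

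The Cox model lists age and sex, and adjusting for them removed the attenuation in simulation. That stands as a matter of method. But APACHE II predicted mortality, month of discharge, hospital-based zone and acute diagnostic category have no evident value for a population control. Fitted to both groups as listed, the model is undefined for controls; fitted to patients alone, it cannot give an effect of ICU care. It does not clearly rescue the comparison.

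The 1000 are people who return every questionnaire, so a cohort that includes deaths must be larger, and the absolute standard errors above are probably pessimistic. The quotient √(1 + d1/d0) is unaffected.

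A reader might also infer that more controls come at almost no cost. The documents say nothing about the cost or availability of extra ONS controls, and they are not needed for the fix.

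**Conclusion.** The point holds as a correctable inefficiency in a stated aim. It does not invalidate the plan.

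- On the ratio scale, one sampled control per patient inflates the standard error about 2.4 times under the assumed 100 to 200 and 20 to 40 deaths, and 1.7 to 6.0 times across the other cases tabulated. All of this is conditional on assumed control mortality.
- A reader might take this as a large loss of precision generally. It is not: on the absolute scale patient sampling error dominates, and the loss is about 2 to 10% at 35% mortality, more at lower mortality.
- A reader might also suppose that ignoring the matching widens the interval. The simulations show otherwise. It attenuates the hazard ratio, mildly at small ratios and more at large ones, and makes the test conservative.

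**What to change.** Amend Planned analyses in two places.

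1. Stratify the log-rank test by age band (for example five-year bands) and sex, not by individual pair. In any Cox model comparing patients with controls, use the same strata and keep only covariates defined in both groups. Put the ICU-specific covariates in a patients-only model.
2. Report observed and expected deaths, with expected deaths from national age-, sex- and calendar-year-specific rates. Give the ratio with a 95% confidence interval, and draw the expected survival curve beside the patients' Kaplan-Meier curve. Keep the 1:1 controls as a supporting analysis.

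The cost is some analysis time and obtaining the rates; no extra patients are needed.

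The limits should be stated in the plan. Population rates carry no individual covariates, include some people who were treated in ICU, and do not supply the condition matching promised in the Aims. Nor does the change settle when follow-up should start: Planned analyses counts from ICU admission, while the inclusion criteria require survival to hospital discharge. That needs its own correction before either comparison is read.
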